The pathological mechanism of TBE is unclear. After injury, the neuroinflammatory cascade that is considered an important mechanism of TBE promotes the rapid progression and progressive aggravation of TBE.^[20]^ Highly expressed inflammatory factors in the damaged brain tissue [e.g., C-reactive protein (CRP) and interleukin-6 (IL-6)] are released into the blood circulation; then, the degree of nerve tissue damage and the prognosis can be judged according to the serum levels of inflammatory factors.^[21]^ Many clinical studies have provided evidence of the anti-inflammatory effects of acupuncture. For example, Chen et al^[22]^ have concluded that acupuncture could downregulate the levels of inflammatory factors (IL-6 and IL-8) in patients with TBI, whereas Cho et al^[23]^ have found that acupuncture could reduce CRP levels in patients after craniotomy.

TBE is a complex and changeable pathological process, and the appropriate target cohort of treatment should be selected in order to measure the effectiveness of acupuncture. Here, we present the study protocol for a RCT to examine whether complementary acupuncture on acute-phase TBI is effective compared against the conventional treatment alone in patients with TBE. In addition, the study will also observe whether acupuncture is associated with an anti-inflammatory effect and a reduction in the volume of brain edema.

We present the following article in accordance with the SPIRIT reporting checklist.

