#### Secondary outcomes

2.6.2

The secondary outcomes are wake-promoting rates, changes in the GCS (Baseline GCS is used as the basis for grouping), the volume of TBE calculated by CT scan (i.e., the volume of brain contusions and pericontusional edema), and the serum levels of CRP and IL-6 measured at four different time points (baseline and days 7, 14, and 28 after treatment). Another secondary outcome, the Modified Barthel Index (MBI), will be measured at the beginning of treatment, at the end of 28-day treatment, at the 6-month and 12-month follow-up after injury.

Calculating the volume of TBE, including the volume of brain contusions and pericontusional edema, by CT scan with the help of 3D Slicer software (version 4.8.1) might reduce the subjective impact of quantifying brain edema. 3D Slicer is a free, open source, and multi-platform software package widely used for medical, biomedical, and related imaging research; it has been jointly developed by multiple institutions and has been supported by the National Institutes of Health in the United States.

The Human IL-6 ELISA kit (Wuhan Fine Biotech Co., Ltd., China) or the Human C-Reactive Protein ELISA kit (Head Office in China Beckman Coulter Commercial Enterprise (China) Co., Ltd. Shanghai, China) will be used to determine the concentrations of IL-6 or CRP in the samples, and the data will be analyzed. Collected samples will be centrifuged for 15 minutes at 1000 × *g* and stored in a freezer at −80 C until they are ready for processing and analysis. Samples will be discarded after the analysis. The timepoints for assessment are listed in Table 2.

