### Sample size calculation

2.9

Because the data available for patients with TBE who receive early acupuncture treatment are limited and inconclusive, we will perform a single-blind RCT in which the control group will receive conventional treatment and the study group will receive additional acupuncture as an adjuvant therapy. The primary outcome will be dichotomized GOS (poor recovery = GOS 1∼3; good recovery = GOS 4∼5) at 6 and 12 months of follow-up after the injury. According to our previous pilot study, the change of GOS (good recovery rate) in the study group was shown to be 80% (n = 12), and that in control group was 50% (n = 12). Sample size was calculated using the Power Analysis and Sample Size (PASS) software package (version 15, NCSS, Kaysville, UT), with a 2-sided significance level (α = 0.05), a power of 80%, and chi-squared tests to assess the difference in rates between the 2 groups. Thus, a total sample size of 80 participants (40 per group) will be recruited, allowing for 10% loss during follow-up.

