### Statistical analysis

2.10

After a patient has been randomly assigned, the outcome measures will be collected even if the trial treatment is interrupted or not given. The data used will include the method of the last observation carried forward or the method of the worst observation carried forward.^[26]^ That is, this study will analyze the data with the full analysis set.

The statistical analyses will be performed by a blinded researcher. According to the intention-to-treat principle, all the data will be analyzed using the SPSS statistical software package (version 20.0, IBM SPSS Statistics, IBM Corp, Somers, NY). Baseline characteristics will be described and compared. Continuous variables subject to normal distribution will be presented as the mean ± standard deviation; continuous variables not subject to normal distribution will be expressed as the median and interquartile range; and categorical variables will be described as the frequency and percentage.

GOS, wake-promoting rates, and adverse events rates will be compared using the chi-squared or Fisher's exact tests. GCS and MBI scores will be compared between the 2 groups by *t* test with a 95% confidence interval. The results of the volume of TBE and the serum levels of CRP and IL-6 between the 2 groups will be compared using either a generalized linear mixed model or the *t* test, and repeated contrast tests will be conducted to account for time differences in each group. If the data are not normally distributed, nonparametric methods will be used. For all analyses, the results with a *P* value less than .05 will be considered statistically significant. The clinical efficacy should be determined in the evaluation of clinical significance.

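### For oedema volume, CRP and IL-6 the only time-specific test named is a within-group contrast, which cannot show whether acupuncture alters the course

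*Protocol article*

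**What the plan says.** All references are to the protocol article.

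- **Aim (Introduction).** Beyond the main comparison, "the study will also observe whether acupuncture is associated with an anti-inflammatory effect and a reduction in the volume of brain edema". The Discussion repeats this aim. It is a comparative question: acupuncture plus conventional treatment against conventional treatment alone.
- **Measurements (section 2.6.2).** Oedema volume, CRP and IL-6 are secondary outcomes, "measured at four different time points (baseline and days 7, 14, and 28 after treatment").
- **Between-group analysis (section 2.10).** The results for these three outcomes "between the 2 groups will be compared using either a generalized linear mixed model or the *t* test".
- **Time analysis (section 2.10, same sentence).** "repeated contrast tests will be conducted to account for time differences in each group".
- **Threshold (section 2.10).** "For all analyses, the results with a *P* value less than .05 will be considered statistically significant".

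The section names no contrast that compares change over time between the arms, and it does not say how the choice between mixed model and t test will be made.

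**The concern.** The null hypothesis of a repeated contrast inside one group is that the mean does not change between two visits in that group. All patients receive treatment to lower intracranial pressure and other conventional care (section 2.5.2), so both arms may well change over 28 days with or without acupuncture. The contrast can then be significant in either arm for reasons unrelated to the randomised comparison.

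The plan puts these contrasts under the same significance threshold as everything else, so they are inferential rather than descriptive. They yield one P value for each arm. A fall that is significant with acupuncture and not significant without it is easily read as an anti-inflammatory or anti-oedema effect, although the difference between the two falls has not been tested. At stake are the trial's mechanistic conclusions, which the authors want to use as groundwork for larger trials.

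**Working it through.** **Inputs from the protocol article**

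- Four time points (section 2.6.2) give 3 adjacent-visit contrasts per arm for each of 3 outcomes. I take the repeated contrasts to be adjacent-visit comparisons.
- 40 patients per group with 10% loss (section 2.9): 40 × 0.9 = 36 evaluable per arm.
- Threshold P < .05 (section 2.10), taken as two-sided as in section 2.9.

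**The plan's own figure.** The plan gives no figure for these three outcomes. Its sample size is for dichotomised GOS, 50% against 80%. The unpooled normal formula gives (1.960 + 0.842)² × (0.5 × 0.5 + 0.8 × 0.2) / 0.3² = 7.849 × 0.41 / 0.09 = 35.8, so 36 per arm. Then 36 / 0.9 = 40 per arm, or 80 in total. This reproduces the stated 80 and supports 36 as the evaluable number.

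**Assumptions, because the protocol gives no values**

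- SD of 1 at each visit, and correlation ρ between visits of 0.5 or 0.7.
- The same true fall of d SD between adjacent visits in both arms, so no acupuncture effect.

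**Within-arm contrast.** The SD of an adjacent change is √(2(1 − ρ)): 1.000 at ρ = 0.5 and 0.775 at ρ = 0.7. The noncentrality of the paired t test is d × √36 / √(2(1 − ρ)). At d = 0.3 this is 0.3 × 6 / 1.000 = 1.80, or 0.3 × 6 / 0.775 = 2.32. With 35 degrees of freedom, the noncentral t distribution gives the probability p that one arm is significant. The arms are independent, so the probability that the study group is significant and the control group is not is p(1 − p).

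| Shared fall d (SD) | ρ | Noncentrality | p, one arm | p(1 − p), study group only |
|---|---|---|---|---|
| 0.2 | 0.5 | 1.20 | 21% | 17% |
| 0.2 | 0.7 | 1.55 | 33% | 22% |
| 0.3 | 0.5 | 1.80 | 42% | 24% |
| 0.3 | 0.7 | 2.32 | 62% | 24% |
| 0.4 | 0.5 | 2.40 | 65% | 23% |
| 0.4 | 0.7 | 3.10 | 85% | 12% |
| 0.5 | 0.5 | 3.00 | 83% | 14% |
| 0.5 | 0.7 | 3.87 | 96% | 3% |
| 0.8 | 0.5 | 4.80 | 99.7% | 0.3% |

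Simulation (10,000 trials per setting) agrees. At d = 0.3 one arm was significant in 41.2% (ρ = 0.5) and 61.2% (ρ = 0.7) of trials, and the study group only in 23.9% and 23.8%. The mirror pattern, control group only, is equally likely under these assumptions.

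**Three contrasts on one outcome.** In simulation with ρ = 0.5 and no acupuncture effect, at least one of the three contrasts was significant in the study group and not in the control group in 13%, 63%, 39% and 1% of trials, for shared falls of 0, 0.33, 0.5 and 0.8 SD.

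**Between-arm tests on the same data.** The shared fall cancels in the difference between arms, so the rejection rate should be 5% whatever d is. In simulation the between-arm contrast of change rejected 4.7% to 5.0% of the time, and a between-arm t test at day 28 rejected 4.8% to 5.1%.

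**The case against.** The strongest reply is that the same sentence already plans a between-group comparison. In a randomised trial, a t test between arms at a visit is a valid test of acupuncture, with about 5% false positives in the simulation. A mixed model could also carry a group-by-visit term, and its exact terms may properly be left to a statistical analysis plan that is not shown. This stands: a reader might infer that the plan never compares the arms on these outcomes, and the text does not support that.

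A reader might also infer that within-arm P values will be taken as the acupuncture effect. The protocol does not say so. It gives the contrasts the purpose of accounting for time, and the threshold is a general one. The risk is a misreading that the plan leaves open, not one that it prescribes.

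Nor are the rates in the column for one arm false-positive rates. In those scenarios the arm really does change, so the rejections are correct. They show only that the test answers a different question. The misleading pattern cannot exceed 25% per contrast, since that is the maximum of p(1 − p), and it comes near that ceiling only for moderate shared changes. The equal fall at each interval is assumed, and the Introduction describes early worsening of oedema, so the real course may differ.

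The reply does not remove the point. The protocol positively specifies a within-group test under a significance threshold for the time course of outcomes whose aim is comparative. An analysis plan that followed this text would inherit it, and t tests at each visit plus within-group contrasts would satisfy it.

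**Conclusion.** The point holds in a limited form. A between-group comparison of oedema volume, CRP and IL-6 is planned and is valid. But the only test named for change over time is made within each group, and it cannot show whether acupuncture alters the course.

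Under no acupuncture effect, with 36 per arm and correlation 0.5 to 0.7, a contrast is significant in the study group only in about 24% of trials at a shared fall of 0.3 SD and 12% to 23% at 0.4 SD. It falls to about 3% at 0.5 SD with correlation 0.7 (14% with correlation 0.5) and is rarer for larger falls. The between-arm contrast stays at about 5%. These sizes rest on an assumed SD, correlation and common course. The logical point, that a within-arm contrast does not compare the arms, does not depend on them.

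Only secondary outcomes are concerned. The change is worth making, but it does not threaten the primary result.

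**What to change.** In section 2.10, make the mixed model already named the single analysis for oedema volume, CRP and IL-6, and drop the t-test alternative for them. Specify group, visit and group-by-visit terms and state how the baseline value enters the model. Report the between-arm difference in change from baseline at days 7, 14 and 28, each with a 95% confidence interval. State that the treatment effect is read only from these between-arm contrasts. Show within-group changes descriptively, without P values. The section's nonparametric fallback for non-normal data should follow the same rule.

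The cost is a few lines of text and analysis code. No further patients, visits or samples are needed. What is lost is the within-arm P values, which do not answer the trial's question. The primary GOS analysis and the sample size of 80 stay as they are.

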### Quality control

2.11

The study protocol has been reviewed and revised by experts on neurosurgery, acupuncture, rehabilitation, and statistics several times. Before the trial, all the researchers will be trained to ensure that the personnel involved fully understand the trial protocol and standard operating procedures. All the study data will be recorded on the CRFs. Data will be uploaded and verified by 2 additional researchers who will be unaware of patient allocation. Monitoring and auditing of the clinical trial will be conducted by the DSMB who will verify all documents related to the clinical trial, including CRFs, and monitor whether the clinical trial is conducted in accordance with the prescribed protocols. If any revisions of protocol occur, they must be approved by the ethics committee of the hospital.

### Ethics and dissemination

2.12

The study protocol conforms to the ethical guidelines of the Declaration of Helsinki^[27]^ and is approved by the Ethics Committee of Qionghai People's Hospital, Hainan Province, China (clinical trial plan approval number: QH065). The trial has been published in the Chinese Clinical Trial Register, http://www.chictr.org.cn/edit.aspx?pid=141208&htm=4 (Identifier: ChiCTR2100053794, registered on December 3, 2021). If there are any modifications to the study design, the Ethics Committee will be notified promptly. The purpose and potential risks of this clinical trial will be fully explained to the participants’ relatives (or their legal representatives), from whom informed consent will be obtained.

We will disseminate the results of this study in meetings or publications when the trial is completed.

## Discussion

3

TBE, the most frequent cause of death after TBI, is an independent risk factor for neurological unfavorable prognosis.^[3,4]^ TBE occurs commonly as pericontusional edema of brain contusions, which leads to a life-threatening increase in ICP. In evidence-based medicine, no treatment measures other than craniotomy and mannitol have been recommended for TBE.^[6]^ Thus, more effective and safe strategies to improve the outcome of patients with TBE are urgently needed. As a complementary and alternative therapy, acupuncture has been widely used to treat neurological diseases, and the effect of acupuncture on patients with TBI has been certified by some studies.^[28,29]^

Here, we describe the protocol of a single-center, single-blinded, RCT to determine if the addition of complementary acupuncture for TBE on acute phase is more effective than conventional treatment alone. We also aim to determine whether acupuncture has an anti-inflammatory effect and is associated with a reduction in the volume of brain edema. This RCT selects appropriate participants and controls confounding factors to optimize clinical evaluation of efficacy.

In this RCT of conventional treatments combined with acupuncture for TBE, we chose drug therapy (i.e., mannitol) as the conventional treatment to reduce ICP, because mannitol is commonly used clinically and is recommended by evidence-based medicine. Also, the optimal timing of acupuncture therapy for TBE is unclear. We relied on expert consensus and clinical guidelines that considered the safe and feasible approach when acupuncture therapy started within 72 hours after injury.^[30,31]^

In this study, the acupuncture points were selected based on traditional Chinese medicine theory, our previous pilot study, and summaries of the medical experts’ experiences. For example, the acupuncture points of GV26, PC6, and SP6 were selected on the basis of Shi's Xingnaokaiqiao theory, which has achieved significant effects in the treatment of acute and critical cerebrovascular diseases.^[32]^ In addition, Chen has used the acupuncture points of GV20, GV26, GB20, LI4, and LR3 to treat neurological diseases and achieved satisfactory clinical curative effects in improving brain function.^[33]^

Among the scores measuring functional recovery and quality of life after TBI, GOS is the most reliable, most validated, and most used score in RCTs.^[34]^ We defined the GOS at 6 and 12 months as the primary outcome.

The treatment plans for patients with TBE and the measurement of treatment effect are usually based on evaluating the ICP level at an acute-phase TBI. The ICP measure is commonly estimated by clinical judgment according to neurofunctional evaluation and CT image interpretation.^[18,35]^

This feasibility trial has the necessary optimizing features that may be helpful for future trial designs in TBE. However, some limitations still exist in this study. First, the number of cases is relatively small and is collected from a single center, which may have led to overfitting of the protocol. Second, we are adopting a single-blinding approach; because of the characteristics of acupuncture, the therapists and the participants cannot be blinded in this study. Finally, limiting participation of patients of age 16 to 75 years and with GCS scores of 6 to 12 means that the study results cannot be applied to all patients with TBI.

In conclusion, this pragmatic study protocol will allow us to determine the actual effects of acupuncture during real-life conditions in normal medical practice for TBI. Positive results from our study may lead to insights about a valuable complementary acupuncture option for TBE and could provide pilot evidence for additional and larger RCTs. This study has the potential to change recommendations for acute-phase acupuncture as a treatment for patients with moderate to severe TBI.
